# Enhancing activity, nutrition and mental health in overweight adolescents: Stage 2 Ethics Research Plan

**Aims/objectives of the study**

This study will use a wait-list controlled, staggered entry trial to assess the impact of a multidisciplinary intervention by:

1) comparing sedentary and moderate/vigorous activity before and after participation. We hypothesise that sedentary and moderate/vigorous activity will be improved after the program and this will be maintained at 3, 6 and 12 months post intervention.

2) comparing physical status before and after participation. We hypothesise that adiposity, cardiovascular fitness, muscle strength and power and coordination will be improved after the program and this will be maintained at 3, 6 and 12 months post intervention.

3) comparing food intake before and after participation. We hypothesise that intake of fruits and vegetables will be increased and intake of “extra” foods will be reduced after the program and this will be maintained at 3, 6 and 12 months post intervention.

4) comparing mental health status before and after participation. We hypothesise that mental health will be improved after the program and this will be maintained at 3, 6 and 12 months post intervention.

5) comparing perceived quality of life before and after participation. We hypothesise that quality of life will be improved after the program and this will be maintained at 3, 6 and 12 months post intervention.

We will also explore the influence of adolescent gender, baseline status, readiness to change, self efficacy, emotional eating and parental status and family function on changes in adolescent outcomes. Process evaluation will also be conducted to assess program fidelity, satisfaction and adverse outcomes.

**Background**

**Rationale for focusing on overweight adolescents**

The 2007 Children’s Nutrition and Physical Activity Survey found approximately 25% of boys and 30% of girls aged 9-13 years were classified as overweight or obese [1-2]. It has been suggested that changes to environmental and societal factors such as a decrease in physical activity, an increase in sedentary behaviour and the availability of high fat, high energy food have contributed to the high rates of overweight and obesity [3]. Obesity is seen as problematic in adolescents as it is related to short-term and long-term medical and psychosocial problems.  Short-term difficulties can include physical discomfort, hypertension, orthopaedic problems, sleep apnoea and increased risk of heart disease and Type II diabetes [4].  Psychosocial problems can include social isolation, decreased self-esteem and depression [5-6].

Adolescence has been identified as a critical period for the development of obesity [7]. Obese adolescents are more likely to become obese adults [8].  Longitudinal studies have indicated that individuals who remain overweight from adolescence to adulthood had lower economic, educational and social outcomes than normal weight peers even when initial socioeconomic factors were controlled for [9].

Despite the recognition of adolescence as a critical period in physical and psychosocial development, there is limited scientific interventions\ research with overweight adolescents. Glenny et al. [10] conducted an early meta-analysis of obesity treatment, and reviewed a total of 13 random-control trials with obese or overweight children or adolescents. They only considered studies with a minimum follow-up of 12 months, as maintenance of change was viewed as an important factor in the success of this type of intervention. They concluded there was a significant evidence gap with physical activity, lifestyle change and family involvement identified as promising foci for treatment. More recently, Oude et al. (2009) [11] conducted a Cochrane Review for treatment of obesity with both adolescents and children.  A total of 17 randomised controlled trials were reviewed with a focus on lifestyle interventions targeting physical activity, diet or behaviour therapy oriented treatments specifically for adolescents. Overall they concluded that *‘…family-based lifestyle interventions with a behavioural program aimed at changing diet and physical activity and thinking patterns provide significant and clinically meaningful decrease in overweight in ..adolescents..’*(p17). Whitlock et al. [12] review also concluded that recent evidence supports the efficacy of comprehensive programs of moderate to high intensity (>26hrs contact). A brief review of some of the supporting evidence is presented below (see also Stewart, Reilly & Hughes, 2008 [13]).

**Activity behaviours**

On an individual level, an imbalance between energy intake and energy expenditure can lead to obesity [14]. A change in energy balance is required to achieve weight loss outcomes, by either increasing energy expenditure through physical activity or reducing energy intake or ideally a combination of both. Achieving this outcome in adolescents is further complicated by the need to recognise that growth is still occurring. Kemper et al. [15] conducted a longitudinal study measuring body-mass index (BMI) and lifestyle factors from the age of 13 until 27 years. Their results demonstrated a strong relationship between high levels of physical activity and low body mass. Berkey, Rockett, Gillman and Colditz [16] conducted a large one-year prospective study and found that increased physical activity was associated with decreases in BMI in girls and overweight boys. Increases in sedentary behaviour were associated with increases in BMI.

The research above supports the utilisation of physical activity as a key component in adolescent obesity treatment. Interestingly the results from Anderson et al.,[17] suggested that targeting sedentary behaviour may significantly improve outcomes. Results from a study by Epstein et al. [18] support this proposition. In their randomised controlled trial with 8 – 12 year olds, participants were allocated to a treatment group which either targeted physical activity, sedentary behaviour or both. At twelve month follow-up the sedentary behaviour group had significantly greater weight reduction than the other two groups. These results have yet to be replicated with adolescent participants.

**Nutrition behaviours**

Obese adolescents appear to consume less well-balanced diets with more low nutrient, high energy foods consumed. Spear et al. [14] reviewed the evidence on various dietary prescriptions and concluded that there may be a relationship between increased overweight or obesity in adolescents and decreased fruit or fruit and vegetable consumption. Adolescents are low consumers of fruits and vegetables but consume 36 percent of their energy intake from unhealthy food or “junk food” [2, 19]. Available evidence supports interventions which provide education on nutritional and energy values of foods, and encouraged a healthier and more balanced diet, whilst discouraging dieting or restrictive eating [11]. Interventions that target dietary modification alone appeared to be less effective than those that combined dietary modification and physical activity [20]. Clearly an intervention strategy targeting both diet and physical activity and the motivators and barriers to weight maintenance would appear to be the best approach.

**Attitudes**

Spear et al. [14] argued that whilst most effective treatments for childhood obesity included both dietary and physical activity interventions, behavioural aspects also need to be considered. Behaviour modification treatment involves utilisation of behavioural change strategies aimed at changing thinking patterns and actions, which may be in relation to dietary intake, physical activity or other aims. Oude et al. [11] identified 12 studies that explored behavioural modification treatment with adolescents and performed a meta-analysis with four studies that fitted the criteria for this type of analysis. The meta-analysis revealed significant reduction in BMI at the end of treatment and maintenance of weight changes at 6 month follow-up compared with controls. The strategies that appeared most beneficial in behavioural management techniques were monitoring, goal-setting and contingency management [14].

Daley et al. [21] conducted a randomised control study with obese children aged 11-16 years. Participants were assigned to an exercise plus therapy condition, where motivation to change and behavioural modification were addressed whilst engaged in aerobic exercise, an exercise condition, involving light body conditioning only, or no treatment condition.  Participants in the behavioural treatment condition reported greater levels of self-esteem, although there were no changes to depression scores or BMI. Whilst behaviour therapy based treatment can produce positive outcomes, difficulties remain in relation to small weight reductions, maintenance and psychosocial problems. Brennan et al. (2008) argued that cognitive behaviour therapy (CBT) may be important in improving interventions for obese adolescents. Brennan et al. [22] conducted a randomised control study where CBT for weight loss was delivered on an individual basis to adolescents with their parents. They reported positive changes in weight loss and psychosocial measures. The current evidence supports the proposal that short-term CBT, in addition to behavioural strategies to address physical activity and eating behaviour, can provide positive outcomes in relation to weight changes and psychosocial stressors.

**Family**

Garn et al. [23] found that the offspring of two obese parents had an 80% probability of being obese compared with a 10% chance for offspring of two lean parents. Whilst it is acknowledged that there may be a genetic factor to the development of obesity, parental attitudes and behaviour also appear to have an impact [1]. Furthermore parents often remain responsible for food choices within the home for adolescents [1].

Stewart et al. [13] report that the expert consensus is that parents’ engagement in obesity treatment with children and adolescents is important. A recent example is where Andrews et al. [24] assessed 201 mothers and found maternal attitudes, social norms and perceived behavioural control predicted behavioural intentions and these in turn predicted parental tracking of child food behaviours.

**Summary**

Given the large proportion of Australian adolescents currently overweight it is clear current practices are insufficient. In order to avoid the expected trajectory to morbid obesity [25] Australian [26] and international [27] researchers have recommended urgent evaluation of interventions targeting overweight adolescents.

The recent evidence of the lack of efficacy of a GP delivered intervention for children [28] and promising early results from two multi-disciplinary community-based overweight adolescent programs [29-30] aligns with earlier expert panel recommendations for “comprehensive multi-disciplinary intervention…[to] encourage healthy behaviours while using techniques to motivate patients and families..” [14] (p.254). The most recent systematic reviews [11-12] have confirmed this approach. Oude et al [11] identified critical issues for future research including: interventions for different levels of severity (we will target overweight and mildly obese), strategies for long-term maintenance (we will work with communities and families to identify sustainability factors), family characteristics which promote success (our process assessment with collect this), adolescent psychosocial factors which influence change (our broad evaluation framework will capture this), resource-effective methods for delivering interventions in different settings (we will evaluate this in metropolitan and regional community settings), and potential harm and benefits of intervention (we will monitor adverse effects as well as health outcomes).

Given the current evidence and strong recommendations for urgent action on this ‘global epidemic’ [11] this project will build on published evidence, recent pilot work and team experience to refine and implement a multi-disciplinary family-centred community-based intervention intended to influence the physical activity, nutrition and psychosocial behaviours of overweight adolescents

**Methods**

**Intervention:** The intervention will be based on a successful pilot program conducted by the research team that in turn was based on current evidence for the management of adolescent obesity [11, 30-31] and the successful “Fitmatters” program conducted in a tertiary clinical setting. Key strategies of the intervention were: focus on healthy behaviours rather than weight management, multi-disciplinary facilitators and family involvement. The intervention also focussed on the psychosocial aspects of being overweight and was based on to the families’ readiness to change using the PRECEDE-PROCEED Framework [32-35]

The program consists of an 8 week multi-disciplinary family-centred intervention focussed on improving activity, food and attitude habits. Groups of up to 12-15 adolescents and their parents attended 2 hour sessions twice weekly. On each occasion adolescents participated in a 45 minute exercise class involving aerobic, strength and coordination stations. Adolescents also participated in education sessions covering moderate physical activity, sedentary behaviours and diet. Tailored feedback on fitness, screen time and diet were provided to each adolescent. Other sessions provided support and group counselling on setting goals, overcoming set-backs and dealing with cognitive and emotional issues. Adolescents were set ‘homework’ relevant to the stage in the program – for example keeping a diary of TV programs watched. Parents participated in education sessions covering the same issues as the adolescents, sometimes with their child and sometimes separately. Parents also gained informal support from other parents and staff in ‘walk and talk’ sessions, which itself modelled a way of building more activity into their day. Parents were also given practical training in buying and preparing healthy food during a supermarket visit and cooking classes. All sessions were run during school term but out of school hours. A brief program outline is shown in Table 1 (each week has two rows – one for each program day). We intend to include regular contact (SMS, phone, mail) to assist motivation and maintenance of effects after the 8 weeks.

# Study design: A wait-list controlled, staggered-entry cohort design will be used. Participants will be recruited and given an initial assessment then reassessed after 3 months waiting (just before starting the program). The dual pre-participation assessments will provide a within-subjects control period. Follow-up assessments will be conducted immediately after completing the program (3 months after second pre-program assessment) and at 3, 6 and 12 months post program.

Cohorts of 12-15 overweight adolescents and their parents will be progressively recruited over the study period. Cohorts are expected to start in Perth metropolitan October 2011, February 2012 and April 2012. The staggered start will control for external seasonal and public event confounders to intervention effects.

Table 1. Project community engagement (*), implementation cohorts (shaded) and follow up assessments (x)

| **Cohort** | **2011** | | | | **2012** | | | | **2013** | | | |
| --- | --- | --- | --- | --- | --- | --- | --- | --- | --- | --- | --- | --- |
|  | 1/4 | 2/4 | 3/4 | 4/4 | 1/4 | 2/4 | 3/4 | 4/4 | 1/4 | 2/4 | 3/4 | 4/4 |
| South metro | * | * | recruit | waitlist | S1 | S2 | S3x | x | x | x | x |  |
| East metro | * | * | recruit | waitlist | N1 | N2 | N3x | x | x | x | x |  |
| Regional | * |  | * | * | recruit | waitlist | R1 | R2 | x | x | x | x |

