**Evaluation**

There is substantial agreement that interventions for overweight young people need to be evaluated in terms of process and outcome and not just immediate impact (Livingstone et al 2007) to understand not only how much the intervention works but why and for whom.

**Process evaluation:** A broad process evaluation will be conducted in line with the recent framework for mandatory evaluation to ensure well informed public policy decisions [38] and recommendations by the recent Cochrane review for obesity interventions [11]. Questionnaire surveys of participants, focus groups of participants and program facilitators are anticipated [39].

Program fidelity will be assessed through observations of sessions, review of program notes and focus groups with program staff [40]. Program dose will be assessed by attendance records. Barriers to participation will be explored through participant/parent surveys including reasons for non attendance and gaining reasons for drop out from those who do not complete the program [41]. Participant satisfaction will be assessed with a validated tool [42] along with focus groups. Monitoring will also be conducted for potential adverse effects, specifically: changes in linear height, disordered eating, and psychological well being [11].

**Impact evaluation:** Immediate impact of the intervention will be assessed by comparing the changes over the 3 months between pre program assessment and immediately post program assessment with any changes over the 3 months ‘wait-list’ period between initial assessment and pre program assessment.

The primary impact measures will be changes in: 1) leisure time spent in light and moderate/vigorous physical activity; 2) leisure time spent in sedentary activity; 3) number of weekly serves of fruit and vegetables and 4) number of weekly serves of extras.

Secondary impact measures will include: readiness to change state, exercise self efficacy and food self efficacy, meeting of sedentary screen time, vigorous physical activity and key diet target behaviours.

**Outcome evaluation:** The longer term changes in behaviour (same variables as short term impact), as well as physical and mental well being and family functioning, will be assessed by comparing changes between assessments at baseline and at 3, 6 and 12 months post intervention.

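### The post-program assessment is called immediate yet set 3 months after the pre-program assessment, around an 8-week program; the timing statements cannot all hold

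*Protocol*

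**What the plan says.** The Intervention paragraph under Methods fixes the program length: "The program consists of an 8 week multi-disciplinary family-centred intervention focussed on improving activity, food and attitude habits". It also announces an intention to keep contact with families by SMS, phone and mail once the 8 weeks are over.

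Study design sets the visits. After the initial assessment, participants are "reassessed after 3 months waiting (just before starting the program"), which makes the waiting period a within-subject control. The next visit is "immediately after completing the program (3 months after second pre-program assessment"), with further visits 3, 6 and 12 months after the program.

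The Impact evaluation paragraph under Evaluation uses the same timing: "Immediate impact of the intervention will be assessed by comparing the changes over the 3 months between pre program assessment and immediately post program assessment". The comparator is the change over the 3-month wait-list "period between initial assessment and pre program assessment". The measures that depend on this comparison follow directly: "The primary impact measures will be changes in: 1) leisure time spent in light and moderate/vigorous physical activity", then sedentary leisure time, weekly serves of fruit and vegetables, and weekly serves of extras.

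**The concern.** The visit schedule has four elements: an assessment just before the program, a program of 8 weeks, an assessment immediately after it, and 3 months between those two assessments. Any three exclude the fourth, and nothing in the protocol explains the difference.

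This matters because the wait-list period is the only control comparison described. Each adolescent's change over the program is judged against the same adolescent's change while waiting, so the two periods need to be equally long, or their lengths need to be taken into account. Staff scheduling a visit must choose between the two instructions. One choice changes what the visit measures; the other changes the length of one side of the primary comparison. Staggered cohorts could also choose differently.

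**Working it through.** **Inputs**

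- Program length: 8 weeks (Methods, Intervention).
- Second pre-program assessment: just before the start (Study design).
- Post-program assessment: immediately after the end, and 3 months after the second pre-program assessment (Study design; Evaluation, Impact evaluation).
- Wait-list interval: 3 months (same places).
- Longest stated measurement window: 7 days of accelerometry (Moderate/Vigorous Physical activity).
- Conversion: 365.25 / 12 / 7 = 4.348 weeks per month.

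**Step 1. Can the stated 3 months be reproduced?**

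- 3 months = 3 x 4.348 = 13.04 weeks.
- From the protocol's own elements, the interval is 8 weeks = 8 / 4.348 = 1.84 months.
- Unexplained difference: 13.04 - 8 = 5.04 weeks.

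The figure is not reproduced. The protocol allots no time for assessments around the program, so any allowance is my assumption:

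| Total allowance | Interval | In months | Short of 3 months by |
|---|---|---|---|
| 0 weeks | 8 weeks | 1.84 | 5.04 weeks |
| 2 weeks (one 7-day window each side) | 10 weeks | 2.30 | 3.04 weeks |
| 4 weeks | 12 weeks | 2.76 | 1.04 weeks |

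**Step 2. If the visit is held at 3 months.** Both intervals are 13.04 weeks, so unequal length causes no bias. The visit falls up to 5.04 weeks after the last session. It then measures early maintenance, possibly after some of the SMS, phone or mail contact has taken place.

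**Step 3. If the visit is held when the program ends.** Let E be the program effect and D the drift per 3 months, assumed linear. For an interval of w weeks:

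- program-period change = E + D x w / 13.04
- wait-list change = D
- unscaled difference = E - D x (1 - w / 13.04)

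The error is therefore:

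- w = 8: -(5.04 / 13.04) x D = -0.39 x D
- w = 10: -(3.04 / 13.04) x D = -0.23 x D
- w = 12: -(1.04 / 13.04) x D = -0.08 x D

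The protocol gives no value for D. For illustration only, at 8 weeks an assumed D of 0.10 SD gives an error of about 0.04 SD, and 0.20 SD gives about 0.08 SD. The error has the opposite sign to D.

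**Step 4. Direction.** For activity and for fruit and vegetables, benefit is an increase, so upward drift would understate it and downward drift would overstate it. For sedentary time and extras, benefit is a decrease, so upward drift would overstate it and downward drift would understate it.

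**Step 5. Follow-up clock.** Measured from the pre-program assessment, the visit 3 months after the program falls at 8 + 13.04 = 21.04 weeks if counted from the end of week 8. If counted from a post-program visit held at 3 months, it falls at 13.04 + 13.04 = 26.09 weeks (unrounded). The same 5 weeks carry through to the 6- and 12-month visits.

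**The case against.** The strongest reply is that the protocol states the 3-month interval twice and matches it to the wait-list period. On that reading the comparison is balanced and only the word immediately is loose. Quarterly scheduling in Table 1, sessions confined to school term, and time for 7-day accelerometry and three-day food records could account for part of the gap. The later visits are described as post program and post intervention, which points to program end. The Analysis plan specifies a multi-level mixed model with adjusted mean changes, and the way time enters that model may properly be left to a statistical analysis plan.

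Much of this stands. Equal intervals are the likelier intention, and 0.39 is an upper limit that applies only if visits take place at about 8 weeks. A reader might infer that the primary comparison is biased by 39% of the wait-list change; the documents do not support that, because both intervals are given as 3 months. Nor do they say that one raw change is simply subtracted from the other, since the plan speaks of comparing changes and of a model.

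What does not stand is the view that nothing needs correcting. No passage offers scheduling or assessment time as the explanation, and even a 4-week allowance leaves a week over. Visit timing is a protocol matter, and an analysis plan cannot undo visits already held at inconsistent times. The anchor of the later visits is clear only if program end and the post-program visit coincide, which under a 3-month visit they do not.

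**Conclusion.** The point holds as an unresolved contradiction in the timing of the visit that carries the four primary impact measures. Its certain size is about 5 weeks between 8 and 13 weeks, or about 3 weeks if two weeks are assumed for assessments.

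The consequence depends on which instruction is followed. On the literal and likelier reading, the comparison is balanced but does not measure immediate impact. On the other reading, an unscaled comparison is off by up to -0.39 x D, or about -0.23 x D at 10 weeks. That result rests on linear drift of unknown size, and its direction differs between the measures to be raised and those to be lowered. It is a conditional risk, and no bias has been demonstrated.

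**What to change.** Reconcile the Intervention paragraph, Study design and Impact evaluation so that they give one schedule:

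- State one target week and a window for the post-program visit, counted from the pre-program assessment.
- State whether the 3-, 6- and 12-month follow-ups count from program end or from that visit.
- Preferably keep the wait-list and program intervals equal, and describe the visit as 3 months from program start instead of immediate. No scaling for unequal length is then needed.
- If the visit is instead held at program end, require visit dates to be recorded and use actual elapsed time in the mixed model, so that unequal intervals are not compared raw. State the linear-drift assumption this adds. With only two pre-program assessments the design cannot check it, so this is the fallback.

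The preferred route costs protocol wording and agreement on a visit window. The fallback also needs a visit-date field, which the protocol does not mention, and an extra modelling assumption.

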## Analysis plan

Process evaluation will use descriptive statistics and qualitative analysis.

Impact and outcome evaluation will use a multi-level mixed modelling approach for the hierarchical data collected over the one-year observational period (repeated measurements of individuals nested within families.) Estimates of change in outcomes over time periods will be adjusted for potential confounders of age, gender, maturation level, IRSAD and parental education levels. All change estimates will be presented as adjusted mean change with corresponding 95% confidence intervals. Non-normally distributed data will be appropriately transformed as necessary, and statistical models checked for unduly influential outliers. All data analysis will be performed utilising current statistical software (Stata/IC 10.1 for Windows, Statacorp).

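### Staggered starts control seasonal confounding only in part, because the planned starts are not balanced over the year and the model has no calendar term

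*Protocol*

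**What the plan says.** The Study design section of the protocol names season and public events as threats and gives the remedy: "The staggered start will control for external seasonal and public event confounders to intervention effects". On timing it says: "Cohorts are expected to start in Perth metropolitan October 2011, February 2012 and April 2012". Table 1 in that section lays out three program blocks for each of two metropolitan areas (quarters 1, 2 and 3 of 2012) and two regional blocks (quarters 3 and 4 of 2012), eight in all.

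The comparator is each participant's own wait: "The dual pre-participation assessments will provide a within-subjects control period". The order and spacing are fixed. The second assessment follows a 3-month wait and comes just before the program. The post-program assessment comes 3 months after that.

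Under Evaluation, immediate impact is defined as "comparing the changes over the 3 months between pre program assessment and immediately post program assessment with any changes over the 3 months" of waiting. The Analysis plan describes a mixed model for repeated measurements within individuals within families, and says: "Estimates of change in outcomes over time periods will be adjusted for potential confounders of age, gender, maturation level, IRSAD and parental education levels". No term for calendar time, season or cohort appears there or elsewhere in the protocol.

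**The concern.** Wait and program are consecutive quarters in a fixed order, so within any one cohort season is completely confounded with period. Staggering helps by averaging over cohorts that start at different times of year. That average cancels season only if the starts are spread evenly over the year. Otherwise calendar time has to be modelled. The planned starts are not evenly spread, and the model as described does not contain calendar time.

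The listed covariates do not fill the gap. Gender, area-level socioeconomic index and parental education are fixed, or nearly so, over the six months in question, and as main effects they cannot confound a within-person contrast. Age and maturation do change over time, but they do not track season.

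At stake are the primary impact measures: leisure-time activity, sedentary time, and serves of fruit, vegetables and extras. If these vary with season, part of that variation would be read as program effect, or would mask it.

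**Working it through.** The plan gives no figure for seasonal bias, so there is none to reproduce.

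**Inputs.** From Study design: 3-month wait, 3-month program interval, the October, February and April starts, and the Table 1 blocks. From Evaluation: the contrast (post − pre) − (pre − initial), and an expected change of 10% in each primary behaviour. Assumed: season is an annual sinusoid S(t) = A·cos(2π(t − φ)/12) with unknown amplitude A and phase φ; cohorts are of equal size; each Table 1 block is preceded by its own 3-month wait.

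**Step 1, one cohort.** For a program starting at month t, the contrast picks up

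[S(t+3) − S(t)] − [S(t) − S(t−3)] = S(t+3) − 2S(t) + S(t−3).

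The outer two points are six months apart and cancel, leaving −2S(t). The worst case over phase is 2.00A.

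**Step 2, several cohorts.** The bias is −2 times the mean of S over the start months. Its worst case is 2A·R, where R is the length of the mean of unit vectors placed at the start months on a 12-month circle. Its root-mean-square over phase is 2A·R/√2.

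| Starts | R | Worst phase | Root-mean-square |
|---|---|---|---|
| One cohort | 1 | 2.00A | 1.41A |
| October, February, April | 1/3 | 0.67A | 0.47A |
| Table 1, six metropolitan blocks | 2/6 | 0.67A | 0.47A |
| Table 1, all eight blocks | √2/8 = 0.177 | 0.35A | 0.25A |
| Even over four quarters | 0 | 0 | 0 |

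- *October, February, April:* October and April are opposite and cancel, so one of three remains. If these dates mean entry to the wait-list, the program starts move to January, May and July. January and July cancel, and R is again 1/3.
- *Eight blocks:* program quarters are Q1 ×2, Q2 ×2, Q3 ×3, Q4 ×1. The net imbalance is one along Q3−Q1 and one along Q2−Q4, so R = √(1² + 1²)/8.

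**Step 3, how much staggering removes.** Against 2.00A, the metropolitan starts remove 1 − 0.67/2 = 67% of the worst case, and the eight blocks remove 1 − 0.354/2 = 82%.

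**Step 4, scale.** With A assumed at 10-15% of the mean, the eight-block worst case is 0.354 × 10 = 3.5 to 0.354 × 15 = 5.3 points. The root-mean-square is 0.25 × 10 = 2.5 to 0.25 × 15 = 3.75 points. The expected change is 10%.

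**Step 5, can a calendar term be fitted?** I fitted cohort-by-visit means by least squares with cohort effects, linear time in study and a program effect, with and without season terms.

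- *October, February, April (nine cells):* adding annual sine and cosine gives seven parameters and full rank. Sinusoidal bias falls from up to 0.67A to 0. The variance factor of the program effect goes from 2.00 to 2.13, about 7% more.
- *Table 1 schedule:* sine and cosine cost about 2% in variance (eight blocks) or 5% (metropolitan only). Quarter effects cost about 9% or 25%.

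**The case against.** Staggering is itself a design control. With starts even over four quarters the bias would be zero without any season term, so the missing term is not an error in principle. That stands, and it is why the point is partial control.

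The covariate list is headed as potential confounders and need not be exhaustive, and a separate statistical analysis plan could add a season term. This has some force. But the protocol makes a positive claim that the staggered start delivers the control, names season as a confounder itself, and then gives an adjustment set without it. The claim is too strong for the starts it plans. Having the listed covariates in the model is no error.

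Amplitude and phase are not in the protocol, so size and sign are unknown. Waits for most Table 1 blocks are inferred from the 3-month rule, because the table shows only one explicit wait-list quarter per site. Both points stand as limits on the size.

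A reader might infer more in three ways, none of which the document supports.

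- *That seasonal change passes undiminished into the estimate.* It does not: the worst case falls from 2.00A to 0.67A or 0.35A.
- *That the bias could match the expected effect, since 0.67 × 10-15% is about 7-10 points.* That figure applies only if the analysis were confined to the metropolitan cohorts, at the worst phase. No metropolitan-only analysis is specified, and Table 1 includes regional cohorts.
- *That waits spanning school holidays bias the contrast, given "All sessions were run during school term but out of school hours".* A holiday between two assessments does not in itself alter either one. Only the assessment weeks matter (seven days of accelerometry, three days of food records), and the protocol does not say when these fall. The sentence is also in the past tense, in a paragraph that mixes the existing program with plans.

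**Conclusion.** The concern holds in limited form. The Study design section overstates what staggering achieves. With the planned starts and no calendar term in the described model, seasonal confounding is reduced by about two thirds (metropolitan starts) to four fifths (all eight blocks) of its worst case, and the rest remains in the impact contrast. The residual is up to 0.67A or 0.35A respectively. This rests on an annual sinusoid, equal cohort sizes and, for the eight blocks, a 3-month wait before each. The size in points depends wholly on the assumed amplitude, and at some phases there is no bias at all. The plan may therefore yield a biased estimate; the document does not show that it will, or in which direction.

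**What to change.** In the Analysis plan, add calendar-time terms for the date of assessment next to the period terms: either an annual sine and cosine pair, or quarter-of-year effects. In Study design, reword the claim to say that staggering reduces seasonal confounding and, together with this adjustment, allows it to be controlled. These terms address season; they do not by themselves deal with one-off public events.

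The program effect stays identified because cohorts overlap in calendar time. On the Table 1 reading, some cohorts wait while others are in the program in each of the first three quarters of 2012.

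The cost is two parameters (sine and cosine) or three (quarters), and modestly wider confidence intervals: variance up about 2-7% with sine and cosine, or 9-25% with quarter effects. The last range means intervals about 4-12% wider (√1.09 = 1.04, √1.25 = 1.12). No extra visits or participants are needed, but the analysis needs the date of each assessment. The protocol does not say that dates are recorded, though its timed visit schedule implies it.

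An indicator for assessments in school-holiday weeks is optional. It matters only if assessments fall in holidays, and whether it could be estimated was not checked.
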